# Enhancing Mental and Physical Health of Women through Engagement and Retention (EMPOWER) 2.0 QUERI: study protocol for a cluster-randomized hybrid type 3 effectiveness-implementation trial

**DOI:** 10.1186/s43058-022-00389-w

**Published:** 2023-03-08

**Keywords:** Hybrid effectiveness-implementation trial, Mixed methods, Evaluation, Implementation strategies, Replicating effective programs, Evidence-based quality improvement, Diabetes Prevention Program, Telephone Lifestyle Coaching, Reach Out, Stay Strong Essentials, Stages of Implementation Completion

## Abstract

**Background:**

Women Veterans are the fastest-growing segment of Veterans Health Administration (VA) users. The VA has invested heavily in delivering care for women Veterans that is effective, comprehensive, and gender-tailored. However, gender disparities persist in cardiovascular (CV) and diabetes risk factor control, and the rate of perinatal depression among women Veterans is higher than that among civilian women. Challenges such as distance, rurality, negative perception of VA, discrimination (e.g., toward sexual and/or gender minority individuals), and harassment on VA grounds can further impede women’s regular use of VA care. Enhancing Mental and Physical Health of Women through Engagement and Retention (EMPOWER) 2.0 builds on work to date by expanding access to evidence-based, telehealth preventive and mental health services for women Veterans with high-priority health conditions in rural and urban-isolation areas.

**Methods:**

EMPOWER 2.0 will evaluate two implementation strategies, Replicating Effective Practices (REP) and Evidence-Based Quality Improvement (EBQI), in supporting the implementation and sustainment of three evidence-based interventions (Virtual Diabetes Prevention Program; Telephone Lifestyle Coaching Program; and Reach Out, Stay Strong Essentials) focused on preventive and mental health care for women Veterans. We will conduct a mixed-methods implementation evaluation using a cluster-randomized hybrid type 3 effectiveness-implementation trial design to compare the effectiveness of REP and EBQI on improved access to and rates of engagement in telehealth preventive lifestyle and mental health services. Other outcomes of interest include (a) VA performance metrics for telehealth care delivery and related clinical outcomes; (b) progression along the Stages of Implementation Completion; (c) adaptation, sensemaking, and experiences of implementation among multilevel stakeholders; and (d) cost and return on investment. We will also generate implementation playbooks for program partners to support scale-up and spread of these and future evidence-based women’s health programs and policies.

**Discussion:**

EMPOWER 2.0 provides a model for mixed-methods hybrid type 3 effectiveness-implementation trial design incorporating evaluation of performance metrics, implementation progress, stakeholder experience, and cost and return on investment, with the ultimate goal of improving access to evidence-based preventive and mental telehealth services for women Veterans with high-priority health conditions.

**Trial registration:**

ClinicalTrials.gov, NCT05050266. Registered on 20 September 2021.

**Supplementary Information:**

The online version contains supplementary material available at 10.1186/s43058-022-00389-w.

Contributions to the literature
Relatively few studies have compared the effectiveness of implementation strategies for achieving the rollout of evidence-based interventions across large healthcare systems.Conducting a rigorous comparison of clinical benefit, cost and return on investment, and time to achieving implementation associated with two different implementation strategies—Replicating Effective Programs (REP) and Evidence-Based Quality Improvement (EBQI)—can directly support evidence-based policy and resource allocation decisions.This study protocol provides a model for mixed-method implementation evaluation in a large healthcare system.

## Background

As the fastest-growing segment of users in the Veterans Health Administration (VA) [1], the number of women Veterans receiving care in the VA is expected to increase by 73%, from 9.3 to 16.4%, between 2015 and 2043 [2]. In anticipation of this increase, the VA has invested heavily in providing effective, comprehensive, and gender-tailored care [3, 4] to address women Veteran patients’ unique and complex healthcare needs [5–7]. However, gender disparities persist in cardiovascular (CV) and diabetes risk factor control in and out of the VA [8, 9]. Also, the prevalence of many mental and physical comorbidities, including perinatal depression, obesity [10], and cardiovascular disease [11], remains higher among women Veterans than among civilian women [12]. Historically, women Veterans have had a high rate of attrition from VA care due to distance and low ratings of VA care quality [13]. Negative perceptions of VA care [14], comorbid mental health issues [15], discrimination based on sexual and/or gender minority identities [16], harassment on VA grounds [17], and distance and rurality [18, 19] are cited barriers in women’s regular use of VA care. Thus, improvements are still needed to increase women Veterans’ access to and engagement in convenient, safe, evidence-based, patient-centered care that achieves the VA “lane of effort” of Veterans’ “lifelong health, well-being, and resilience” [20].

Telehealth, or the delivery of healthcare via remote technologies including telephone, video calls, and online, is ideal for addressing existing gaps in care for women Veterans. Barriers to gender-specific care include the low numbers of women Veterans at any single VA location, access barriers due to work, travel times, and school and caregiving responsibilities, particularly for women Veterans living in rural areas. Telehealth can address these barriers by providing flexible, individualized care and reducing travel burden. The evidence suggests that women Veterans stand to benefit from telehealth approaches, particularly in healthy lifestyle change for disease prevention (including increasing physical activity, weight management, smoking cessation, and diet) and reproductive health (including contraception, prenatal care, maternal mental health, lactation, and postpartum care) [21].

Since its inception in 2015, the *E*nhancing *M*ental and *P*hysical health *o*f *W*omen through *E*ngagement and *R*etention (EMPOWER) QUERI 1.0 team has focused on implementing gender-tailored, preference-based care models for women Veteran patients with high-priority health conditions: (1) type 2 diabetes risk, (2) cardiovascular risk, and (3) anxiety and/or depression [22]. In EMPOWER 1.0 studies, women Veterans expressed preferences for gender-specific (women only) care and for telehealth care options [23]. Therefore, we are extending our overarching commitment to improving women Veterans’ engagement and retention in care with our EMPOWER 2.0 Impact Goal to expand access to evidence-based, preventive lifestyle and mental health services delivered by telehealth for women Veterans with high-priority health conditions in rural and urban-isolation areas. To achieve this impact goal, we propose a coordinated program with the following aims:Using two implementation strategies (Replicating Effective Practices [REP] [24] and Evidence-Based Quality Improvement [EBQI] [25]), support implementation and sustainment of three evidence-based practices (EBPs) focused on preventive lifestyle and mental health care for women Veterans across 20 VA facilities (10 with REP, 10 with EBQI), several of which are rural, low-performing in women’s health care, and/or lead sites for high-reliability organization [20].Conduct a mixed methods implementation evaluation using a cluster randomized hybrid type 3 effectiveness-implementation trial design [26]. We will compare the effectiveness of REP and EBQI in improved access to and rates of engagement in preventive lifestyle and mental telehealth services. Other outcomes include (a) VA performance metrics for telehealth care delivery and related clinical outcomes for women Veterans; (b) progression along the *Stages of Implementation Completion* [27]; (c) adaptation, sensemaking [28], and experiences of EBP implementation among multilevel stakeholders [29]; and (d) cost and return on investment [30].Generate implementation “playbooks” [22] for program partners that are scalable and serve as guidance for future implementation of a broader array of evidence-based women’s health programs and policies.

These conceptually and methodologically linked aims will be realized by an experienced multidisciplinary team with a strong track record of collaboration and guided by a Technical Expert Panel of operational and research partners and subject matter experts. We will implement three EBPs: (1) *Virtual Diabetes Prevention Program (Virtual DPP)* [31], an evidence-based lifestyle intervention, emphasizing moderate weight loss, diet, and physical activity, shown to prevent and/or delay progression to type 2 diabetes; (2) *Telephone Lifestyle Coaching Program (TLC)* [32], developed by one of our partners (National Center for Disease Prevention and Health Promotion), which provides evidence-based, individual-level, personalized health coaching focused on wellness and cardiovascular disease prevention; and (3) *Reach Out, stay Strong, Essentials (ROSE)* [33], an evidence-based intervention for prevention of perinatal depression that can be delivered via telehealth. (For detailed background on these EBPs and related health conditions among women Veterans, see Additional file 1.)

## Methods/Design

### Overview of study design

In this 5-year study, we will conduct a cluster randomized hybrid [26] type 3 effectiveness-implementation trial to evaluate the effectiveness of two implementation strategies (REP and EBQI) in supporting the implementation of three evidence-based practices (virtual DPP, TLC, and ROSE) to increase use of prevention-focused telehealth services among women Veterans (Aim 1). Below we describe our three Aims in detail.

### Aim 1: Using two implementation strategies (REP [24] and EBQI [25]), support implementation and sustainment of three EBPs focused on preventive lifestyle and mental health care for women Veterans across 20 VA facilities (10 REP and 10 EBQI sites)

#### Implementation strategies

EMPOWER 2.0 focuses on comparing two evidence-based implementation strategies described below (Table 1).

**Table 1 Tab1:** Implementation strategies: key activities by phase

	Years 1-2.5		Years 2.5-4	Year 5
**QUERI Roadmap**	**Pre-implementation** Identify problem & solution Engage stakeholders Develop measures and data		**Implementation** Implement an intervention Activate implementation teams Monitor implementation progress	**Sustainment** Sustain an intervention Transition ownership to stakeholders Ongoing evaluation and reflection
**REP**	***Pre-conditions***	***Pre-implementation***	***Implementation***	***Maintenance and evolution***
	Ensure fit, identify barriers, draft intervention package	Develop package, pilot test, identify champion, hold orientation meetings	Train staff, provide TA, conduct evaluation, measure fidelity, measure outcomes, share results, discuss sustainability	Change practice to facilitate long-term adoption, prepare package for dissemination, recustomize delivery
**EBQI**	Regional stakeholder planning meetings, formative evaluation	Train local QI champions and team members	Provide practice facilitation, expert review and feedback, monthly across-site calls, technical workgroups, formative evaluation	Foster regional spread, summative evaluation

##### Implementation strategy 1—Replicating Effective Programs (REP)

REP has a strong evidence base in VA health services and implementation research—including in EMPOWER QUERI 1.0 [22, 34]—in promoting uptake of evidence-based pratices [24]. Informed by theories of Diffusion of Innovation and Social Learning, the REP framework consists of four phases: pre-conditions, pre-implementation, implementation, and maintenance/evolution [24]. Careful attention is paid to intervention packaging during pre-conditions and pre-implementation; training, technical assistance, and fidelity assessment during implementation; and re-customizing during maintenance/evolution. During each phase, local context is paramount, with varying deployment of the intervention depending on local priorities, needs, and resources. Our team has comprehensive expertise in REP grounded in implementation of three EBPs across diverse sites in EMPOWER 1.0.

##### Implementation strategy 2—Evidence-Based Quality Improvement (EBQI)

Tested in several VA implementation trials (e.g., of collaborative care for depression, VA’s patient-centered medical home (PACT), Women’s Health PACT), EBQI is a systematic QI method for engaging frontline primary care practices in improvement that introduces “best science” and evidence in the service of operational goals and is supported by a partnership between multi-level, interdisciplinary operations stakeholders and a research team [29]. EBQI is aimed at developing learning organizations through multi-level, cross-discipline engagement with science and data. It draws upon explicit QI support by scientific teams to enable context-tailored evidence-based practices; social science theory on provider/team behavior; and improved use of implementation and QI methods. Application of EBQI in the EMPOWER QUERI 2.0 will focus on identifying (with multilevel stakeholders) context-specific design priorities for the three EBPs. Notably, both EMPOWER 2.0 implementation strategies reflect phased approaches consistent with recommendations of the QUERI Implementation Roadmap (Table 1) [35].

We have selected EBQI and REP because they provide differing approaches to supporting sites with implementation of EBPs: EBQI is a higher-intensity strategy that entails multilevel stakeholder engagement, while REP is a lower-intensity strategy with an explicit process framework for local tailoring. Both strategies have strong evidence of effectiveness and are well-established in VA. As noted in the QUERI Roadmap [35], health systems have already invested in EBQI “to scale up and spread their practices and policies nationally,” but we have yet to understand the conditions in which this investment in a high-intensity strategy is warranted, compared to a low-intensity strategy. Comparing these strategies across multiple sites for three different EBPs (virtual DPP, TLC, and ROSE) will provide data on implementation strategy effectiveness and cost, which will be of direct relevance to leadership in decision-making and investment. Findings will allow a detailed examination of how each implementation strategy supported the implementation of each EBP across varying settings, thereby elucidating a blueprint for matching strategies with EBPs in differing organizational contexts.

*Setting and site selection*: We recruited sites (Fig. 2 below) from the Women’s Health Practice-Based Research Network (PBRN), a network that provides a research infrastructure for investigators seeking to increase inclusion of women in VHA research or conduct multi-site women’s focused research in VHA. Comprised of approximately 70 VA sites that see one-half of women Veteran VA users, the PBRN helps investigators overcome the challenges of multi-site studies through the engagement of Site Leads with established working relationships with local clinicians and facility leadership. Sites were also recruited in collaboration with regional leadership in four regional Veterans Integrated Service Networks (VISNs). Each VISN was selected based on leadership’s interest in the EBPs, priorities for women Veterans’ preventive health, and our history of collaboration.

*Low-performing sites*: Our team has a long history of working with sites to improve women Veterans’ health, including QI efforts in low-performing sites. For the current project, a number of our sites are designated low-performing sites based on site visit assessment data.

*Patient eligibility and selection*: Women Veteran VA users are eligible for each EBP as follows: (1) *Virtual DPP*—overweight/obese women Veterans (BMI≥25 kg/m^2^ [≥23 if Asian]) with history of prediabetes (defined as either an HbA1c 5.7-6.5% or fasting blood glucose 100–125 mg/dL or oral glucose tolerance test 140–199 mg/dL) or history of gestational diabetes (GDM) or high risk on diabetes screening questionnaire. Women will receive invitation letters or be referred to the program by a healthcare provider and self-register with a CDC-recognized virtual DPP provider. (2) *TLC*—all women Veterans (who are not pregnant) are eligible to participate in TLC. Women will be referred to the program by a healthcare provider and will receive an outreach call from contracted health coaches to enroll. (3) *ROSE*—All pregnant women Veterans are eligible. Women will be identified and recruited by the site pregnancy/maternity care coordinator or other women’s health staff. As part of each implementation strategy (REP and EBQI, see below), sites will determine their own locally relevant recruitment strategies to engage 40 women Veterans/site in virtual DPP or TLC, and all interested pregnant women in ROSE.

### Aim 2: Conduct a mixed methods implementation evaluation using a cluster-randomized hybrid type 3 effectiveness-implementation trial design comparing the effectiveness of REP and EBQI in terms of (a) improved access to and rates of engagement in preventive lifestyle and mental telehealth services (primary outcome) and improved VA performance metrics for telehealth care delivery and related clinical outcomes for women Veterans; (b) progression along the Stages of Implementation Completion; (c) adaptation, sensemaking, and experiences of EBP implementation among multilevel stakeholders; and (d) cost and return on investment

#### EMPOWER 2.0 Conceptual Framework

Figure 1 reflects grounding in the Consolidated Framework for Implementation Research (CFIR) [36] and intention to examine implementation and sustainment outcomes that QUERI and operations partners have indicated are of the highest value. CFIR offers a synthesis of theory and constructs from across implementation science. Constructs are organized into five domains (outer setting, inner setting, characteristics of the intervention, characteristics of individuals, and implementation process), which are dynamic and interrelated in producing implementation readiness at the individual and collective (e.g., clinical unit, facility) levels. CFIR is increasingly used to aid in implementation and evaluation planning and is specifically recommended for use in examining predictive factors associated with implementation outcomes [37]. Because it accounts for individual- and setting-level characteristics and acknowledges how interactions between individuals and their larger environment(s) may support behavior change, CFIR provides an ideal framework for delineating multilevel factors in complex health interventions.

**Fig. 1 Fig1:**
[figure not shown]
Conceptual model

##### Cluster-randomized trial of the implementation strategies

*Randomization*: For this cluster-randomized trial, we will randomize sites clustered within four VISNs to either REP or EBQI (Fig. 2). Two VISNs will implement virtual DPP and two VISNs will implement TLC. To ensure adequate number of pregnant women for ROSE, all four VISNs will have the option to implement ROSE for their pregnant patients. With our focus on increasing access to preventive services for women living in rural areas, sites that serve rural Veterans will be selectively recruited. Rural sites tend to be community-based outpatient clinics (CBOCs) as opposed to large VA medical centers (VAMCs), so at least one additional CBOC in each VISN will invited to participate. Because the same leadership team may oversee VAMC and CBOC operations, any VAMC and CBOC that share a leadership team will be randomized as a unit to avoid contamination across implementation strategies. Therefore, a total of 20 individual VA sites (VAMCs or CBOCs) will be included from four VISNs. With the balanced design, half of the sites (*N*=10) will receive REP and half will receive EBQI (*N*=10).

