
**Table ﻿2 Tab2:** Measures for Aim 2a

EBP	Primary outcome	Participation and engagement	Primary impact performance goals	Clinical outcomes and other VA performance measures
Virtual DPP	• # of eligible patients who register at the DPP site (i.e., enroll) • # of eligible patients who participate in virtual DPP and attend at least one session	• Average # of DPP sessions attended^a^ • Proportion who completed ≥3, ≥9 and ≥16 DPP sessions^a^ • Change in reported physical activity^a^ • % weight change at 12 and 24 months	Increase participation in weight management program (e.g., MOVE)	• Overweight/obesity/weight management • Prevalence of prediabetes, diabetes, and incident type 2 diabetes • HEDIS: Hypertension and Diabetes
TLC	• # of provider referrals for TLC • # of patients w/ TLC encounter (enrolled)	• Average # of TLC sessions completed^a^ • % with SMART goal^a^ • % with behavioral change (physical activity; diet: fruit, vegetable, and sugary beverage intake; stress and coping; and weight)^a^	Increase in telehealth encounters for prevention (e.g., Whole Health)	• Overweight/obesity/weight management • Prevalence of prediabetes, diabetes, and incident type 2 diabetes • HEDIS: Hypertension and Diabetes
ROSE [4]	• # of provider referrals for ROSE • # of patients w/ ROSE encounter (enrolled)	• Average # of ROSE sessions completed^a^ • Depression screening	Increase in telehealth care for mental health	• # of patients that return to VA post-partum (utilization of VA health services in the 12 months post-partum) • Mental health/depression

^a^This data will be collected as part of the EBP. All other data will come from CDW

We will include data on-site-, provider-, and patient-level variables from VA administrative data or our operations partners. For the sites, we will include facility type (VAMC or CBOC) and size, women panel size, proportion of women at site, type of comprehensive primary care model for women Veterans [4], number of designated women’s health providers, and urban/rurality. Provider characteristics will include provider type (MD or NP) and whether the provider is a designated women’s health provider. Patient-level controls will include sociodemographic characteristics, comorbidity including diabetes and cardiovascular risk, service-connected disability status, utilization, and the most common ICD-10 codes related to pregnancy status.

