*Data analysis plan for Aim 2a*: We will use generalized linear models to evaluate the effectiveness of the intervention strategies for implementation of the EBPs in increasing women’s participation in telehealth-based preventive care. The models will account for clustering at the site level as well as incorporating site- and patient-level covariates outlined above. The main outcomes will include the composite measures of the proportion of women referred and enrolled in preventive telehealth care services, and the primary independent variable of interest is implementation using REP versus EBQI. We will conduct subgroup analyses by EBP to examine if the effects of the implementation strategies on proportion referred and enrolled vary by EBP (TLC or virtual DPP) as well as evaluate the effect on the *primary impact performance metrics* for telehealth care (weight management programs, Whole Health, and telemental health). In each model, we will examine the potential moderating effects of site-level characteristics (e.g., facility type, size, women’s health care program model, etc.). Adjustment for clustering will be performed using Stata v15, and we will evaluate goodness-of-fit using Mallows statistic (Cp). For DPP and TLC, we will use appropriate generalized linear models to assess weight and behavior change and examine differences by levels of participation (number of sessions completed). For ROSE, we will assess depression scores by levels of participation.

*Power calculations*: We based power calculations on the study’s basic single level of clustering sample design, where sites are randomized to receive either REP or EBQI to implement the EBPs. To detect a moderate effect size in terms of Cohen’s *D* (.26 standard deviations) between REP and EBQI, with 20 sites, and cluster adjustment (ICC=.01) with 80% power we will recruit 40 women per site (total of 800 women). We have considered all 20 sites to be separate clusters in terms of these calculations.

Aims 2b–2d are summarized in Table 3.

**Table 3 Tab3:** Overview of Aims 2b–2d

Method	Timing (per QUERI Roadmap)			Intended analyses
	Pre-implementation	Implementation	Sustainment	
Site tracking log	• Meeting minutes • Templated reflections • Stages of Implementation Completion (SIC)			2b: SIC 2c: Adaptations, experiences of EBP implementation 2d: cost

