It is an innovation and strength of this proposal that we will combine 2b and 2c data sources to link qualitative (via interviews, reflections, etc.) assessments of CFIR constructs with implementation and effectiveness outcomes—including SIC scores for stage, duration, and proportion—for each EBP (virtual DPP, TLC, ROSE) and implementation strategy (REP, EBQI). With the exception of recent work by Palinkas et al., relatively few studies have previously investigated associations between CFIR domains and the stages and timing of implementation milestones achieved [40]. This will enable us to investigate, for example, whether EBQI, a strategy that requires more intensive activity in the initial stages and may thus be slower to reach implementation launch, is associated with improved sustainment, given that sites will be equipped with QI tools beyond the life of the project.

*Aim 2d: Data sources*—In line with current recommendations for budget impact analysis (BIA) for single payers [48] and within VA [49], we will compare costs associated with delivery of usual care with costs for implementation and delivery of our prevention-focused telehealth interventions (virtual DPP, TLC, ROSE) in terms of impact on short-term use of downstream health care resources. For example, we will evaluate whether the cost of implementing the ROSE intervention is associated with cost savings related to a reduction in need for specialty mental health care among women Veterans during the postpartum period.

*Aim 2d: Measures*—Core requirements for BIA include estimates of eligible population, current treatment mix and associated costs, expected treatment mix post-implementation and associated costs, and estimated changes in condition-related downstream costs [50]. Cost estimates for implementation strategies will be informed by site tracking log data (e.g., implementation dose in #hours/per site) as described in *Aim 2c: Data sources*. Healthcare utilization data will be drawn from CDW, as described for *Aim 2a: Data sources*, above.

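### Low-performing status, known from site visit data, is neither a stated balancing factor nor a listed site covariate, which leaves a modest but avoidable chance imbalance between the arms

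*Protocol article*

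**What the plan says.** **Site feature.** Aim 1 in the Background gives low performance in women's health care as a feature of several sites. The paragraph on low-performing sites under Aim 1 in the Methods adds: "For the current project, a number of our sites are designated low-performing sites based on site visit assessment data". The status therefore rests on assessments that already exist.

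**Allocation.** The Randomization paragraph states that "we will randomize sites clustered within four VISNs to either REP or EBQI", that a VAMC and CBOC under one leadership team move together, and that each arm has 10 sites. It names no balancing on performance status. Fig. 2, which shows the site-level randomisation, is not available here.

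**Adjustment.** The covariate paragraph after Table 2 begins: "For the sites, we will include facility type (VAMC or CBOC) and size, women panel size, proportion of women at site". It continues with the women's primary care model, the number of designated women's health providers and urban/rural location. Low-performing status is absent. The analysis plan for Aim 2a then builds its models on the covariates set out there and accounts for clustering by site.

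**Planning values.** The target is .26 SD, with "cluster adjustment (ICC=.01) with 80% power we will recruit 40 women per site (total of 800 women"). On the number of clusters: "We have considered all 20 sites to be separate clusters in terms of these calculations".

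**The concern.** The primary outcomes are referral and enrolment. A site already judged weak in women's health care may plausibly do less well on both, whichever strategy it receives. With 20 sites or fewer allocation units, one draw can easily put more weak sites in one arm. The adjustment for clustering widens the interval to allow for this, but it does not move a shifted estimate back. The listed covariates can do so only as far as they happen to track performance status. At stake are the precision of the REP–EBQI comparison and how convincing it looks if one arm visibly holds most of the weak sites.

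**Working it through.** **Inputs.** From the protocol: 20 sites split 10:10, 40 women per site, ICC .01, target .26 SD, power 80%. Assumed because not stated: two-sided alpha of .05, no dropout, 4 to 8 low-performing sites, and for the blocked case four VISNs of five sites each split 3:2 or 2:3.

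**1. The plan's own figure.** Design effect = 1 + 39 × .01 = 1.39. SE of the contrast = √(2 × 1.39/400) = .0834 SD. Power at .26 SD is 87.7% with a normal reference and 83.9% with t on 18 df. The effect detectable with 80% power is .234 or .247 SD. The stated 800 women is therefore on the safe side under these assumptions and is not at issue.

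**2. How likely is an uneven split?** For K low-performing sites and no blocking, the count is hypergeometric with C(20,10) = 184,756 allocations. The chance of a difference of four or more is:

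- K = 4 (4–0): 2 × 8,008/184,756 = .087
- K = 6 (5–1 or worse): 2 × (6 × 2,002 + 1,001)/184,756 = .141
- K = 8 (6–2 or worse): 2 × (28 × 495 + 8 × 220 + 66)/184,756 = .170

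With VISN blocks and the low-performing sites spread 1,1,1,1, then 2,2,1,1, then 2,2,2,2, the values are about .115, .16 and .20. Blocking by VISN does not remove the problem when such sites are spread out. It helps when they are concentrated: four in one VISN of five can split no worse than 3–1.

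Odd counts give lower figures, because the difference must then be at least five. K = 5 gives 2 × 3,003/184,756 = .033. K = 7 gives 2 × (7 × 715 + 286)/184,756 = .057.

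Shared-leadership units can raise the chance. Assume four pairs and twelve single sites, no blocking, and 6 low-performing sites. If these include one whole pair and four singles, the probability is .24. If they are two whole pairs and two singles, it is .27.

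**3. How large is the shift?** In units of the total SD, the between-site SD is √.01 = .10. A factor present at a share p = K/20 of sites can separate them by at most d = .10/√(p(1 − p)), which would mean that it explains all between-site variance. The shift is d × (difference in count)/10.

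| K | split | largest d | largest shift |
|---|---|---|---|
| 4 | 4–0 | .250 | .100 |
| 6 | 5–1 | .218 | .087 |
| 8 | 6–2 | .204 | .082 |
| 10 | 10–0 | .200 | .200 |

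For 6 sites split 5–1, .087/.26 = .34, about a third of the target. The last row is the ceiling for any site-level factor at this ICC.

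**4. What does adjustment cost?** One added site covariate moves the reference from 18 to 17 df, and power from 83.9% to 83.6% if it explains nothing. Two would give 83.3% on 16 df. If one covariate explained all between-site variance, power would be about 93%. These figures leave aside the degrees of freedom used by the site covariates already listed.

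**The case against.** **Randomisation already deals with it.** Over repeated allocations a chance imbalance is not bias, and its variance is what the adjustment for clustering carries. At ICC .01 the arm difference from all site effects together has an SD of √(2 × .01/10) = .045. This stands, and it makes the point one of precision and balance, not of validity.

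**The detail may be elsewhere.** The randomisation wording can be read as allocation within VISN, Fig. 2 is not shown, and an article often leaves stratification to the full protocol. This stands as far as it goes: a reader might infer that nothing but the number of sites is balanced, and the text does not establish that. Step 2 shows, however, that VISN blocking alone would not settle the matter. The covariates are not left open either. The article lists them and ties the model to that list; the open-ended wording in the analysis plan belongs to the examples of moderators.

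**A shift as large as the target.** A reader might infer that imbalance could imitate the whole .26 SD. At ICC .01 it cannot, since the ceiling is .20 SD. Even a 10–0 split would need an ICC of (.26/2)² = .017. With a difference of four sites, the deficit would have to be .26/.4 = .65 SD, which for 6 sites implies an ICC of roughly .08 to .09. Nothing in the protocol supports such values.

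**Earlier QI work at the sites.** The article speaks of the team's experience, "including QI efforts in low-performing sites", and a reader might infer that some REP sites still hold tools from earlier EBQI or REP work, which would weaken the contrast. The text does not say that any trial site had such work or that sites differ in it. History of collaboration was a reason for choosing every VISN. The remark under Aim 2c that "sites will be equipped with QI tools beyond the life of the project" concerns EBQI sites of this trial after it ends. This reading has no support.

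**Constrained allocation has limits.** If each VISN held two pairs and one single site, only 6 × 2⁴ = 96 allocations with 10 sites per arm and 3:2 or 2:3 splits would exist before any constraint. This stands, and it bears on how tight a constraint can be.

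**Conclusion.** The point holds as a low-cost improvement. The article singles out a site feature known from existing data, states no balancing on it, and omits it from an explicit covariate list. For an even count of 4 to 8 such sites, spread over the VISNs, an imbalance of four or more sites has a chance of about one in eleven to one in five. The shift that a difference of four sites could cause is at most about .08 to .10 SD at the planned ICC, and smaller if the status explains only part of the between-site variance. The conclusion rests on the assumed number and spread of low-performing sites, on the ICC of .01, and on the status predicting referral and enrolment, which the article does not document. It does not show that the comparison is invalid or that the sample size is wrong.

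**What to change.** **If allocation is not yet done:** list the possible allocations within VISN with shared-leadership units kept whole. Keep those in which the arms differ by at most one low-performing site, or by the smallest number the units allow. Draw one at random, and include low-performing status in the primary model.

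**If allocation is done:** add low-performing status to the prespecified site covariates, and report the number of such sites by arm.

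**Cost:** a short listing exercise before allocation, one sentence in the analysis plan and one site-level degree of freedom. No sites or women are added. The downside is a smaller set of admissible allocations, so count them first and relax the constraint if too few remain for a meaningful random draw.
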